## Abstract

**Background:**

A standard low-dosing schedule of rituximab (RTX; 2 × 500 mg or 1 × 1000 mg) is as effective for active rheumatoid arthritis (RA) as the registered dose (2 × 1000 mg). Moreover, several small uncontrolled studies suggest that even lower-dosed treatment with RTX also leads to good treatment response in patients with RA. Retreatment with such an ‘ultra-low’ dose RTX in patients who responded well to RTX induction treatment is of special interest, as long-term use of lower RTX doses may lead to shorter infusion duration, lower risk of adverse events and lower costs. However, the effect of ultra-low dose of RTX has not been investigated using a controlled trial of proper design and dimensions.

**Methods/Design:**

REDO is an investigator driven six-month pragmatic, double-blind, randomised controlled non-inferiority trial on the effects of ultra-low-dose RTX (1 × 500 or 1 × 200 mg) compared to standard low dose (1 × 1000 mg) in RA patients who are being retreated with RTX. A total of 140 RA patients, having reached low disease activity (DAS28CRP < 2.9) after the previous RTX infusion and DAS28CRP < 3.5 at moment of retreatment, are randomised in a ratio of 1:2:2 to 1 × 1000 mg, 1 × 500 mg or 1 × 200 mg. The primary objective is testing non-inferiority of the ultra-low-dose vs. standard low-dose RTX, by comparing mean change in DAS28CRP from baseline to six months to the non-inferiority margin of 0.6. Secondary outcomes over the same period are: function; quality of life; safety; costs; and pharmacokinetics and dynamics as process measures.

**Discussion:**

This study protocol shares characteristics of both early dose finding trials as well as late pragmatic clinical studies. Several choices in the design of this trial are described and possible consequences for RA treatment and expected biosimilar introduction are discussed.

**Trial registration:**

Dutch Trial Register, NTR6117. Registered on 15 November 2016 (CMO NL57520.091.16, 8 November 2016)

**Electronic supplementary material:**

The online version of this article (doi:10.1186/s13063-017-2134-x) contains supplementary material, which is available to authorized users.

## Background

Rituximab (RTX) is a chimeric anti-CD20 monoclonal antibody authorised for use in patients with severe active rheumatoid arthritis (RA) in combination with methotrexate (MTX) when patients have an inadequate response or intolerance to other disease-modifying antirheumatic drugs (DMARDs), including one or more tumour necrosis factor inhibitors (TNFi). Two large systematic reviews confirmed the effectiveness of RTX in patients with RA in combination with MTX compared to MTX alone [1, 2]. In addition, long-term safety has been confirmed up to 11 years, with infection risk comparable to other biological DMARDS (bDMARDs) [3, 4].

The dose-finding phase of RTX has some interesting aspects. Since RTX was originally developed as a treatment for non-Hodgkin’s lymphoma, its optimal dose was initially determined for that indication [5]. The first two studies of RTX in RA indeed used treatment protocols based on experience in the treatment of lymphoma [6, 7]. Both studies were open-label and consisted of a limited number of patients. It was reasoned that RA could be seen as a low-grade lymphoma of synovial tissue, caused by an oligoclonal (instead of monoclonal) proliferation of B cells exhibiting malignant behaviour by destroying local tissues. Using this comparison, patients were treated with a single remission-induction treatment course, identical to that for non-Hodgkin’s lymphoma, combining four weekly RTX infusions of 750 mg/m^2^ with prednisone and cyclophosphamide. The treatment goal was to achieve disease remission by eradication of pathogenic B cells. Only adriamycin was omitted as co-medication to decrease the chance on treatment-related side toxicity. These two open-label case series showed that a single RTX-based treatment course could induce disease remission in a proportion of patients with RA. Although no formal dose-finding efforts were done, Leandro et al. concluded in their uncontrolled study of 22 RA patients that doses below 600 mg/m^2^ were less effective, but this conclusion was based on only four patients. The first randomised controlled trial (RCT) to examine the efficacy of RTX in RA patients aimed at obtaining a treatment regimen without cyclophosphamide instead of dose-finding and used a simplified RTX dosing regimen of 1000 mg on treatment days 1 and 15 [8]. This dose is now the registered dose for treatment of RA patients.

Thereafter, dosing schedules of 2 × 500 mg and 1 × 1000 mg have been tested in several phase-three and phase-four studies; a recent large systematic review showed that these were non-inferior to regular-dose RTX. Therefore, the current recommended RTX doses are 2 × 500 mg or 1 × 1000 mg (standard low-dose RTX) at least every six months. The second infusion is commonly given with an interval of two weeks (e.g. for 2 × 1000 mg) [9]. Although there have been no high-quality strategy studies to establish what is the best retreatment strategy, either fixed six-month interval retreatment or disease activity guided treat-to-target retreatment seem the optimal strategy.

However, even lower doses of RTX may be effective for treatment of RA. In three case studies, ultra-low doses of RTX (1 × 50 to 2 × 100 mg) were surprisingly associated with deep peripheral B-cell depletion and, in general, adequate RA disease control [10–12]. Adding to these observations, a recent small, prospective open label study in 14 RA patients showed that a single dose of 100 mg RTX led to peripheral B-cell depletion in 11 patients (79%) after two weeks [13]. In that study, mean (± SEM) DAS28 score of all patients decreased from 6.2 ± 0.8 at baseline to 2.9 ± 0.8 at 24 weeks after infusion, although two patients needed additional RTX treatment.

The use of ultra-low-dose RTX for retreatment could especially be effective. First, B-cell depletion by RTX can persist during the entire interval between infusions [8, 14]. It was shown that that lower baseline B-cell counts were associated with complete B-cell depletion following a first 500-mg dose of RTX [15]. This suggests that the (partially) persisting B-cell depletion induced by an earlier infusion could reduce the dose of RTX needed for retreatment infusions.

A final argument for possible effectiveness of ultra-low-dose RTX is the fact that similar monoclonal antibodies have been shown to be effective well below the authorised doses for RTX. For ocrelizumab and ofatumumab, two humanized anti-CD20 monoclonal antibodies, it was concluded that doses of 2 × 200 mg and 2 × 300 mg, respectively, provide optimal B-cell depletion as well as the best clinical responses [16]. Although these much lower doses compared to RTX might also be possible due to higher affinity or cytotoxic efficacy of the drug, it lends further credibility to study the efficacy of similar ‘ultra-low’ doses of RTX.

The use of ultra-low RTX could present several advantages over standard low-dose RTX. First, infection risk should be lower, as RTX use is associated with a dose-dependent – although still low – risk of serious infection [17, 18]. Also, shorter infusion duration and less administered drug could lead to less patient burden and perhaps lower risk for infusion reaction [19]. Further, RTX treatment currently is relatively expensive, with costs for low-dose 1 × 1000 mg every six months being in the range of €4000–7000 per year. Although RTX was proven to be cost-effective in patients with an inadequate response to TNFi [20], use of ultra-low doses will further decrease costs and thereby improve cost-effectiveness. A combination of a possible effective dose of 200 mg every six months and expected price reductions due to upcoming availability of a rituximab biosimilar, could result in a bDMARD option availability for under €1000 per patient per year.

The use of an ultra-low dose of RTX might, however, also lead to increased disease activity in the subset of patients whose minimal effective RTX dose is 1000 mg. Therefore, prediction of response to ultra-low-dose RTX would be key to prevent patients from flaring experiencing accelerated joint damage [21]. Interesting baseline (at the moment of considering RTX retreatment) candidates for predicting the chance of good response on an ultra-low dose include higher RTX drug levels, absence of anti-RTX-antibody levels and low peripheral B-cell counts, as it might be hypothesised that these are all indicators for lower RTX need [22].

In conclusion, although the use of ultra-low doses of RTX seems promising, its effects have never been studied in a trial of proper design and size. We therefore aim to perform a RCT to study whether retreatment with one of two ultra-low RTX doses (1 × 200 mg or 1 × 500 mg) is non-inferior to retreatment with the standard low-dose RTX (1 × 1000 mg) for patients with RA who were already successfully treated with standard low-dose RTX. Also, we will analyse whether there are differences between retreatment with ultra-low dose and standard low dose in the occurrence of serious and non-serious adverse events and cost-effectiveness, and we will analyse whether (non-)response to (ultra-)low dose of RTX at six months can be predicted at the moment of initiating retreatment.

## Methods

### Design

The REDO study (REtreatment with Rituximab in RhEmatoid arthritis: Disease Outcome after Dose Optimisation) is an investigator-driven, pragmatic, double-blind, non-inferiority RCT of six months’ duration (Fig. 1, SPIRIT checklist as Additional file 1). The trial is funded by two healthcare insurance companies in the Netherlands, Centraal Ziekenfonds (CZ) and Menzis, and independent from the manufacturer of RTX (Roche). The study is expected to be performed in at least three departments of rheumatology of hospitals in the Netherlands: the Sint Maartenskliniek, and Radboud University Medical Centre (Radboudumc) in Nijmegen; and Reade in Amsterdam. These centres together have approximately 400 RA patients being treated with RTX. Based on an earlier dose-tapering trial and similar inclusion criteria, we expect an inclusion percentage of 40%.

**Fig. 1 Fig1:**
[figure not shown]
SPIRIT figure: trial visits and assessments

RA patients who are scheduled for RTX retreatment with standard low-dose RTX will be randomised into three groups: standard low dose (1 × 1000 mg) or one of the two ultra-low dose intervention groups (1 × 500 mg and 1 × 200 mg). Treatment response is assessed at three and six months (study end); thereafter, the allocation of patients will be revealed and treatment may be continued using any ultra-low or standard low dose of 1 × 1000 mg, at the discretion of the physician and patient in shared decision-making.

This report has been prepared in accordance to the SPIRIT guideline. The final report will follow the CONSORT criteria, including its extension to non-inferiority trials. The full study protocol is available as supplementary material. There are no publication restrictions and publication of the final study results will be performed in peer-reviewed journals as well as to lay press and patient organisations.

Important protocol changes will be communicated to the ethics committee and trial register. Privacy of patients will be protected according to Dutch law, WBP (‘wet bescherming persoonsgegevens’), by using anonymised data and restricting access to patient identification logs.

### Objectives

The primary objective of the REDO trial is to compare the difference in efficacy between two ultra-low doses (1 × 200 mg and 1 × 500 mg) and standard low dose (1 × 1000 mg) of RTX retreatment on the change in DAS28-CRP, compared to a pre-specified non-inferiority margin of 0.6 DAS28 points, at three and six months. Therefore, the study has four primary endpoints. Although we are aware that patients are sometimes treated with longer intervals than six months, showing non-inferiority at six months is relevant, for ultra-low RTX dose with at least six-month intervals is still a lower cumulative dose as standard low-dose 1000 mg every 9–12 months.

The main secondary objectives are: to assess the difference in efficacy between the two ultra-low dose interventions for the same outcomes; to compare the proportion of patients with a DAS28-CRP < 2.9 (low disease activity), DAS28-CRP < 2.4 (remission) and remission according to Boolean ACR/EULAR criteria at three-month and six-month follow-up; to assess the between-group differences in the change in functioning (HAQ-DI) and quality of life (EQ5D-5 L); and to compare proportion (cumulative incidence and incidence density) of patients developing (treatment-related) adverse events in each study group over the duration of the study, with special attention to infusion-related adverse events and infections. Furthermore, the cost-effectiveness of both ultra-low RTX doses and the conventional low dose are compared for the six-month study period. For prediction modelling, baseline factors (including RF/ACPA status, CD19+ B-cell count, serum RTX, serum anti-RTX) will be tested for associations with the outcome of DAS28-CRP low disease activity state at six months.

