### Interventions

Patients allocated to the standard low-dose group will receive a (blinded) single 1000 mg RTX infusion according to the standard protocol for infusion of rituximab. Patients allocated to the ultra-low-dose groups will receive 500 mg or 200 mg. This dose will be diluted to the same volume as the standard low-dose infusion to ensure the blinding of the study, all premedication and procedures are identical to the standard low dose. Of note, the possible advantage of shorter infusion times cannot be assessed in our study, because this would lead to patients and healthcare providers being unblinded.

It is aimed to leave all other rheumatic treatment unaltered as much as possible during the study period. However, all treatment decisions are left to the discretion of the treating physician and (changes in) use of paracetamol (acetaminophen), tramadol, non-steroidal anti-inflammatory drugs (NSAIDs), oral corticosteroids and DMARDs are all allowed during this study to ensure good care. During each visit, patients are asked about the use of these medications. Suggested treatment in case of clear loss of response is escape treatment with an extra dose of 1 × 1000 mg RTX. This can be done without unblinding, since the authorised dose of RTX is 2 × 1000 mg per six months and no patients will exceed this dose as the maximum study dose is 1 × 1000 mg.

We have determined several medication changes that are defined as ‘treatment failure’. These changes are: receiving an extra dose of RTX within the six-month study period; receiving another bDMARD (thus switching to another type of bDMARD); and using corticosteroids in a dose > 10 mg/day. Starting a concomitant conventional synthetic (cs)DMARD during the study period is not considered a treatment failure. The reasoning behind this is that all included patients will have received these csDMARDs before, with little effect on their RA, and the concomitant csDMARD is generally given as an adjuvant to increase the effectiveness of RTX.

In case of treatment failure, the patients will remain in the study, but the last measure of disease activity and other outcomes will be used as outcome employing a ‘last observation carried forward’ strategy.

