#### Assessments

At baseline, several characteristics of the patients will be measured, including demographics, disease and treatment characteristics. Also, possible predictors for response to ultra-low-dose RTX from peripheral blood will be collected, including (anti-)RTX drug levels and peripheral CD19 counts. Thereafter, visits will be performed at three and six months and when necessary in between (Fig. 1).

Several measures on disease activity will be collected during the study. The DAS28-CRP is a validated and widely accepted measure for RA disease activity and will be used as a primary outcome measure. It consists of four components: 28 tender joint count; 28 swollen joint count; CRP (mg/L); and patients VAS assessment of global disease activity (0–100) [26]. Remission is defined as DAS28-CRP < 2.4 and low disease activity by DAS28-CRP < 2.9 [32]. In addition, patient VAS assessment of pain, rheumatologist VAS assessment of global disease activity, acute phase reactants (CRP and ESR) and the OMERACT patient flare questionnaire are collected. To measure functioning of patients, the HAQ-DI, a validated instrument that is widely used in rheumatology is applied [33]. Quality of life is assessed using EQ5D-5 L, which is a validated instrument and comprises five questions and a visual analogue self-rating scale [34].

Adverse events are assessed at every visit during the study period and classified according to the Common Toxicity Criteria (CTC) [35]. In addition, we focus explicitly on infusion reactions and infectious events. Patients are asked to complete a short questionnaire after the RTX infusion on the occurrence of infusion-related adverse events. Medication use is charted using data from the electronic patient records on the use of DMARDs, corticosteroids and NSAIDs.

Costs will be calculated from a societal perspective. We will include the cost of outpatients’ clinic visits and telephone consultations, travel expenses for patients, costs of hospitalisation due to RA, costs due to health-related work absence and costs of medication during the six-month study period.

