**Table 1 Tab1:** Total trial sample size at various correlations between endpoints

SD change	r	Sample size 1000 mg arm	Total trial size (5 x sample size in 1000 mg arm)
0.9	0.17	26	130
0.8	0.35	24	120
0.7	0.5	20	100
0.6	0.63	16	80

To protect for a too optimistic correlation, we therefore choose a total trial size of 130 and this is further increased to 140 patients to account for patient drop-out.

Primary analyses will be done per protocol (PP), as this is the most conservative approach for a non-inferiority study. In addition, analyses will be performed on an intention-to-treat basis (ITT). For PP analysis, we will include patients who have received the study medication and completed follow-up of six months or until treatment failure (and last observation of disease activity carried forward).

The primary endpoints will be tested using 95% confidence intervals based on linear regression with the change in DAS28-CRP as outcome, dose group as determinant and baseline values of DAS28-CRP as covariate (ANCOVA).

To find predictors (including age, sex, disease duration, RF/ACPA status, CD19+ B-cell count, serum RTX, serum anti-RTX), patients will be categorised into responders (DAS28-CRP < 2.9 at six months and no treatment failure) and non-responders (all other patients). The absolute number (and thus also proportion) of responders will determine the number of predictors that is admissible for analysis, according to the rule of ten-events-per-variable given that predictors are predetermined. Univariate logistic regression analysis will be performed for the admissible predictive factors, with a deliberately liberal *p* < 0.20 as selection criterion. Univariately significant variables are entered in a full multivariate logistic regression model, that is step-wise reduced until all *p* < 0.20. Internal validation and shrinkage will be performed using a bootstrapping procedure with 1000 repetitions. Performance of the multivariate predictive model will be evaluated using discrimination (area under the receiver operator curve) and calibration (calibration slope, calibration plot and Hosmer-Lemeshow test).

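### Carry-forward after treatment failure can count a failed patient as in low disease activity or remission in the secondary arm comparisons, and the prediction outcome is worded in two ways

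*Protocol article*

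**What the plan says.** **Arm comparison.** The Objectives section lists as a main secondary aim "to compare the proportion of patients with a DAS28-CRP < 2.9 (low disease activity), DAS28-CRP < 2.4 (remission"), and also "remission according to Boolean ACR/EULAR criteria at three-month and six-month follow-up". Treatment failure is not mentioned. The Assessments section likewise defines the states by score alone: "Remission is defined as DAS28-CRP < 2.4 and low disease activity by DAS28-CRP < 2.9".

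**Treatment failure.** The Interventions section defines failure by medication changes: "receiving an extra dose of RTX within the six-month study period", a switch to another biological, or corticosteroids above 10 mg/day. These patients stay in the study, and "the last measure of disease activity and other outcomes will be used as outcome", by last observation carried forward (LOCF). The statistical section repeats the carry-forward of disease activity for the per-protocol set.

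**Prediction outcome.** In the Objectives section, baseline factors "will be tested for associations with the outcome of DAS28-CRP low disease activity state at six months". In the section on sample size and statistical analyses, patients are split into "responders (DAS28-CRP < 2.9 at six months and no treatment failure) and non-responders (all other patients").

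**The concern.** There are two linked problems.

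1. The prediction outcome has two wordings. One is a disease state given by the score; the other is that state and the absence of treatment failure. A patient who failed with a last value below 2.9 is a case under the first and a non-case under the second.

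2. The carry-forward rule is general and makes no exception for yes/no endpoints. Applied to the secondary proportions, it lets a patient who needed extra rituximab or a switch count as having achieved low disease activity or remission, provided the last recorded value was low. An arm with more failures then keeps some of them as successes.

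The direction matters. The Background section itself says that ultra-low dosing might raise disease activity in some patients. If failures are more frequent at 500 mg or 200 mg, the secondary proportions will look more alike than they should, which flatters the lower doses. Readers are likely to set these proportions beside the mean-change result.

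**Working it through.** The plan gives no expected rate, margin or sample size for these proportions, so there is no stated figure to reproduce. The check is a reading of the text followed by an illustration.

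**Step 1: one patient under each rule.** Take a patient with a three-month DAS28-CRP of 2.5 who then receives extra rituximab, with no further score recorded before that dose.

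| Use | Rule in the text | Six-month status |
|---|---|---|
| Arm comparison (Objectives, with the carry-forward rule in Interventions) | carried value 2.5 is below 2.9 | in low disease activity |
| Prediction, as worded in Objectives | low disease activity state | in low disease activity |
| Prediction, as defined in the statistical section | below 2.9 and no failure | non-responder |

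**Step 2: can this patient exist?** Yes. Failure is triggered by medication, not by a DAS28-CRP threshold. The Patients section requires low disease activity after the last infusion and a current DAS28-CRP of at most 3.5. Scheduled visits are at three and six months only, with extra visits as needed. The last value before failure can therefore be a low baseline or three-month score.

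**Step 3: size of the shift.** Let f_T and f_C be the failure rates in an ultra-low-dose arm and the 1000 mg arm, and s the share of failures whose carried value is below 2.9, taken as equal in both arms. Compared with counting failures as not achieved, carry-forward changes the difference (ultra-low minus 1000 mg) by

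shift = s × (f_T − f_C).

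This is positive, in favour of the lower dose, whenever f_T > f_C.

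Inputs from the plan: 140 patients at 1:2:2, so 140/5 = 28 in the 1000 mg arm and 56 in each ultra-low-dose arm.
Assumptions, not in the documents: f_T = 15%, f_C = 5%, s between 20% and 80%, and a low disease activity rate of 75% for the standard error.

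- s = 20%: 0.20 × (0.15 − 0.05) = 0.02, or 2 points. Patients reclassified in an arm of 56: 56 × 0.15 × 0.20 = 1.7.
- s = 80%: 0.80 × 0.10 = 0.08, or 8 points. Patients reclassified: 56 × 0.15 × 0.80 = 6.7.
- Standard error of the difference: √[0.75 × 0.25 × (1/28 + 1/56)] = 0.100, or 10 points. The shift is thus 0.2 to 0.8 standard errors.

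**Step 4: where s might lie.** If the carried value is always baseline, and baseline is normal with the plan's SD of 0.7, cut at 3.5, with an assumed mean of 2.0, 2.3 or 2.6, the share below 2.9 is 92%, 84% or 74%. If a flare visit is recorded first, the share is much lower. The text does not say whether the carried value is taken before or at the failure, hence the wide range.

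**Step 5: effect on the reported difference.** Assume 70% low disease activity among non-failures in both arms, with the same failure rates. Counting failures as not achieved gives 0.70 × 0.85 − 0.70 × 0.95 = −0.07. Adding the shift gives −0.04 at s = 30%, −0.02 at s = 50% and 0.00 at s = 70%.

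**The case against.** The strongest reply has four parts.

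- **A state and a responder outcome are different things.** A prediction model may use a stricter outcome than a descriptive proportion. This stands. A reader might infer that the plan defines low disease activity and remission in two contradictory ways throughout. The documents do not support that: the responder definition covers only DAS28-CRP below 2.9 at six months, for prediction. Nothing in the text gives a second definition of DAS28-CRP remission, Boolean remission or three-month status. The direct mismatch is confined to the wording of the prediction outcome.

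- **The article does not state how the secondary proportions are analysed.** Also true. That carry-forward governs them follows from the general rule, and the full protocol or an analysis plan may say more. But the rule covers disease activity and other outcomes without exception, so this is a stated rule with an unwelcome consequence and not merely a missing detail.

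- **Counting failure as not achieved is a choice.** A patient can exceed 10 mg/day of corticosteroid for reasons unrelated to RA and still have a low score. This is a real cost of the proposed rule and a reason to show both versions.

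- **The upper magnitudes are unlikely.** Escape treatment is suggested for clear loss of response and extra visits are provided for, so the carried value may often be a flare score above 2.9. This weakens the 8-point figure. It does not remove the problem, because no score is required at the time of failure.

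**Conclusion.** The point holds in a limited form. The two wordings of the prediction outcome disagree and should be aligned. Separately, the general carry-forward rule, applied as written, lets treatment failures count as successes in the secondary comparisons of low disease activity and remission. The resulting bias is towards no difference if the lower doses fail more often. With equal failure rates and equal shares of low carried values, the difference does not shift.

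The size cannot be derived from the documents. Under an assumed 15% against 5% failures it runs from about 2 points (20% of failures with a carried value below 2.9) to 8 points (80%), against a standard error of about 10 points. The lower end is the more plausible if flare visits are usually recorded.

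A reader might also infer that the non-inferiority conclusion is compromised. This point does not show that. The conclusion rests on four mean-change tests in fixed sequence, and the proportions have no margin, no power and no place in that sequence. The primary ANCOVA and the sample size are unaffected.

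**What to change.** Before unblinding, in the protocol or analysis plan:

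1. Reword the prediction outcome in the Objectives section to match the statistical section: DAS28-CRP below 2.9 at six months and no treatment failure.
2. For the between-arm proportions (low disease activity, DAS28-CRP remission, Boolean remission), count a patient with treatment failure before the visit as not achieving the state at that visit. For six-month low disease activity this is the failure rule the plan already uses for responders. For remission and for three months it is an extension, offered as an improvement and not as the repair of a contradiction.
3. Report the score-only proportions with carry-forward as a sensitivity analysis, and state whether the carried value is the one before or at the failure.

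This needs no new data or patients and changes no clinical procedure. The cost is somewhat lower reported rates in all arms, including for patients who exceed 10 mg/day of corticosteroid for reasons other than RA.
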